## **24.0 Ethical, Legal and Administrative Aspects**

### **24.1 Ethics Committee**

The study can only start after full and written approval of the protocol and all addenda has been obtained from the local Independent Ethics Committee. The Independent Ethics Committee must be informed of all subsequent, substantial protocol amendments issued by the sponsor. The investigator will provide reports to the Ethics Committee at intervals stipulated in the Ethics Committee guidelines. The MATCH study has been reviewed by the Dulwich Research Ethics Committee.

The study as detailed within this research protocol (**Version 4.0 dated 19 Nov 2019**), or any subsequent amendments will be conducted in accordance with the UK Policy Framework for Health and Social Care Research, the World Medical Association Declaration of Helsinki (1996) and the current applicable regulatory requirements and any subsequent amendments of the appropriate regulations”

### **24.2 Data Monitoring and Ethics Committee (DMEC):**

A DMEC is not planned for this study as the Trial Steering Committee consider that this Observational non-interventional study is at low risk of identifying any new unexpected events. All patients are receiving current standard clinical care, and the metomidate PET CT is non-invasive, and has been previously performed, without serious adverse events, in >300 patients during the last 10 years. All SAE's will be reported to the Trial Steering Committee.

### **24.3 Critical Endpoints Committee**

This will consist at least one physician (Endocrinologist and/or Hypertension specialist), at least one Pathologist and a PET Nuclear Medicine Specialist. They will be independent of those involved in the patients' care, including the pre-operative and post-operative assessments. They will assess the pre-operative investigations (AVS and PET CT) without knowledge of outcome from surgery, and vice versa. This committee will meet every 3-6 months.

### **24.4 The Steering Committee**

Trial Steering Committee (TSC): is chaired by Sir [name] and includes three other independent members, [name], [name]. The three lead investigators [name], [name] and [name] are also members. Observers from the EME Programme are invited to attend in person or by teleconference. A patients' representative has been identified and will be included. The TSC will aim to meet twice yearly.

## **25.0 Data Handling**

The Robertson Centre for Biostatistics at Glasgow University will act as the Data Centre for the trial. It will be responsible for the development of a web-based electronic case report form (eCRF) system for recording trial data at the study sites.

The eCRF will include sections relating to each trial contact with the patient.

### **25.1 Data Capture**

Study data will be recorded via remote data entry into a web-based electronic case report form (eCRF) developed for the study. A manual for eCRF use will be provided for all trial sites. Data entry into the eCRF will be performed either by the investigator or documented designee. The investigator will confirm electronically the completeness and correctness of eCRF completion.

A reason will be supplied for any subsequent changes made to submitted eCRF data.

### **25.2 Data Collection and eCRF**

A Patient Identification List will be created containing personal data such as the name, gender and date of birth of all study subjects, together with their assigned study number. This list does not form part of the eCRF, and will be stored securely at the study site. This is to enable later identification of the study subjects. However, the eCRF data will be anonymous, identifying study subjects by only their assigned study number.

Section 6 details the various data recorded during the course of the trial. These data will all be entered directly into the eCRF, with the exception of the following, which will be recorded electronically and transmitted separately to the Data Centre.

- Baseline visit 12-lead ECG result

### **25.3 Data Management.**

Whenever possible, data will be entered into the eCRF directly online. If this is not possible, data will be entered and stored in password protected shared area. Where USB sticks are used to store information they will need to be encrypted and stored by CI delegated MATCH researcher. All information electrocardiograms etc will be stored by subject number only. At the end of the study all data will be archived according to sponsor SOP for up to 20 years.

The Robertson Centre for Biostatistics, University of Glasgow is responsible for all data management for the trial data. Data management will be in accordance with the Robertson Centre's SOPs.

#### **25.4 Record Retention**

ICH/GCP guidelines require that the investigator or the institution maintains all Case Report Forms and all source documents that support the data collected from each participant plus all trial documentation. Measures will be taken to prevent accidental or premature destruction of these documents. Essential documents must be retained for at least 20 years.. It is the responsibility of the sponsor to inform the investigator when these documents no longer need to be retained. If the responsible investigator retires or leaves the institution responsibility for the documentation must be transferred to a person who will accept their custody.

#### **25.5 Record Archival**

The study data and documentation will be archived in accordance with the relevant regulatory requirements and site SOPs.

### **26.0 Quality Control and Assurance**

This clinical study will be conducted in compliance with the protocol, GCP and the applicable regulatory requirements.

#### **26.1 Direct Access to Source Data and Documents**

According to GCP, the trial investigators will permit authorised third parties access to the trial site and medical records relating to trial subjects. This will include, but not necessarily be restricted to, access for trial-related monitoring, audits, Ethics Committee review and regulatory inspections.

#### **26.2 Monitoring**

Monitoring of centre may be undertaken by a trained study monitor or monitors, to verify the completeness and correctness of the study documentation.

### **26.3 Audits**

The sponsor reserves the right to audit trial sites, subject to giving a suitable period of notice (minimum period of notice 10 working days).

### **26.4 Inspections**

Any study site may be audited by the relevant legal/ regulatory authorities.

## **27.0 Data Protection**

Study data will be protected in accordance with the UK data protection legislation. All study data held electronically from participating study sites will be anonymised. Data will only be identified by the subjects unique study identifier.

The Patient Identification List (linking study number to patient identity) will be stored securely at the study site.

### **27.1 Administrative agreements and protocol adherence**

This observational study will be conducted in accordance with the declaration of Helsinki including all revisions.

Protocol violations comprise any deviation from the procedures defined in the protocol, any missed assessments, and non-compliance with study medication. The investigator should make considerable effort to ensure protocol adherence, or to correct any protocol violations that occur.

All protocol violations should be documented, and any major protocol violations should be reported immediately to the study co-ordinator and Chief Investigator.

If a protocol deviation is required in order to eliminate an immediate hazard to a study participant, this should be documented, indicating the form of deviation, and the reason that this was necessary.

## **27.2 Protocol Amendments**

Neither the investigators nor any personnel involved in the study conduct may alter the study protocol. Protocol amendments will only be made under exceptional circumstances, and only with full agreement of the study Trial Steering Committee. Any protocol amendments agreed will be recorded in writing. All protocol amendments will be notified to all study sites and involved study personnel.

## **28.0 Funding**

The MATCH study is supported by funding from the NIHR EME project number **EME Project number: 14/145/09**.

### **28.1 Insurance**

Queen Mary University of London is sponsoring this study and has arranged for suitable indemnity cover to be in place. Cambridge University as the manufacturer of 11-C metomidate will insure the product. Cambridge University Hospitals NHS Foundation Trust at which the 11-C metomidate PET CT scan is to be undertaken will provide suitable indemnity cover for the procedure.

### **28.2 Publication Policy**

Publications will be supervised by the British Hypertension Society Research Committee. This committee will determine the authorship of each paper using CONSORT guidelines.

### **28.3 Case Payments**

Investigators will only be reimbursed for any study-related expenses.

## **30.0 APPENDICES**

### Abbreviations

|            |                                                    |
|------------|----------------------------------------------------|
| AE         | Adverse event                                      |
| ACTH       | Adrenal                                            |
| ARB        | Angiotensin receptor blocker                       |
| ARR        | Aldosterone renin ratio                            |
| ACEI       | Angiotensin converting enzyme inhibitor            |
| AVS        | Adrenal Vein Sampling                              |
| BAH        | Bilateral adrenal Hyperplasia                      |
| BP         | Blood pressure                                     |
| BHS        | British Hypertension Society                       |
| BHF        | British Heart Foundation                           |
| CETO [18F] |                                                    |
| CCB        | Calcium Channel Blocker                            |
| eCRF       | electronic Case Report/Record Form                 |
| DBP        | Diastolic blood pressure                           |
| ECG        | Electrocardiogram                                  |
| HCG        | Human chorionic gonadotrophin                      |
| ICH        | International Conference on Harmonization          |
| IEC        | Independent Ethics Committee                       |
| IRB        | Institutional Review Board                         |
| IVRS       | Interactive voice response system                  |
| IV         | Intravenous                                        |
| MDT        | Multidisciplinary Team                             |
| MR         | Mineralocorticoid receptor                         |
| NICE       | National Institute for Clinical Excellence         |
| o.d.       | Omnia die/once a day                               |
| PI         | Principal Investigator                             |
| PET        | Positron electron tomography                       |
| PH         | Primary hyperaldosteronism                         |
| PHA        | Primary Hyperaldosteronism                         |
| p.o.       | Per os/by mouth/orally                             |
| SAE        | Serious adverse event                              |
| SBP        | Systolic blood pressure                            |
| SUSAR      | Suspected unexpected serious adverse drug reaction |

## **31.0 PHARMACOGENETIC RESEARCH**

DNA repositories from studies so patients may gain early benefits from the rapid advances in DNA technology in tailoring therapy or reducing side effects. It is already possible to study more than a million markers or single nucleotide polymorphisms across the genome. By the time our study is finished, it may be financially as well as technically feasible to sequence every gene in the genome.

## **32.0 Study Population and Assessment**

Prior to subject participation, specific informed consent for this procedure will be signed by the patient. This research is voluntary and if a patient refuses pharmacogenetic participation they will not be excluded from the clinical study.

A 10ml sample of whole blood will be taken into an EDTA tube following informed consent. Although it is best to take the sample at the beginning of the study, it may be taken any time throughout the study. The tube label will identify subjects only by study number. No personal details will be recorded on the tube, and only designated study members will be able to link DNA analyses to the anonymised clinical data collected during the study. Samples will be stored securely at study sites before shipment to St Bartholomew's London and other sites will be invited during progress of study if required and ethics will be updated .

The named study team members at each site will hold a link between study number and patient name, as is required to permit monitoring and audit of patient records. This link will be used if a subject wishes to withdraw their sample from analysis, subjects can request destruction of their sample and any data extracted from it and pharmacogenetic consent withdrawal form will be completed and signed by the patient. It will record confirmation that the sample has been destroyed following site destruction Trust policy..

Pharmacogenetic research is likely to continue following completion of the clinical study. As is standard for most large-scale genetic studies, samples will be held indefinitely in view of the large amount of potential data they contain and the length of time it might take to mine this data. As the potential uses of these samples cannot be fully predicted at this point, the Informed Consent Document stipulates that samples might also be used for research purposes unrelated to the focus of this clinical study.

If a subject withdraws from the study other than not attending follow up and has not asked for pharmacogenetic destruction, research will continue as stated in their informed consent.

### **33.0 CALCULATION OF PROPOSED SAMPLE SIZE**

The table below shows potential outcomes from the two separate investigations in patients recruited to MATCH:

| Diagnostic Tests |                | Normalisation of plasma renin & aldosterone/renin ratio after surgery (i.e. confirmed unilateral PHA) |            |
|-------------------------|----------------|------------------------------------------------------------------------------------------------------------------|------------|
| AVS              | PET-CT  | No                                                                                                        | Yes |
| Unsuccessful            | Bilateral      | A (=9%)                                                                                                          | B (=0%)    |
| Unsuccessful            | Unilateral     | C (=1%)                                                                                                          | D (=10%)   |
| Bilateral               | Bilateral      | E (=35%)                                                                                                         | F (=0%)    |
| Bilateral               | Unilateral     | G (=1%)                                                                                                          | H (=9%)    |
| Unilateral              | Bilateral      | I (=0.5%)                                                                                                        | J (=3.5%)  |
| Unilateral (c)          | Unilateral     | K (=1%)                                                                                                          | L (=29%)   |
| Unilateral (d)          | Unilateral     | M (=0.25%)                                                                                                       | O (=0.25%) |
| Unilateral              | Unilateral (d) | P (=0.25%)                                                                                                       | Q (=0.25%) |

**Key:** c = concordant; D = discordant (i.e. PET-CT and AVS lateralise to opposite sides)

The accuracy of PET CT will be estimated in patients having surgery, given by:

$$(D+H+I+L+O+Q) / n$$

The accuracy of AVS will be estimated by  $(G+J+L+M+P) / n$

A test of whether these accuracies differ will therefore be a test of whether

$$(D+H+I+L+O+Q) = (G+J+L+M+P)$$

or whether

$$(D+H+I+O+Q) = (G+J+M+P)$$

This can be achieved by a one sample binomial test of whether

$$p = (D+H+I+O+Q) / (D+H+I+G+J+M+O+P+Q) = 50\%$$

Given the estimated proportions given above, the anticipated value of p is 80%. To have 90% power at a 1% significance level to show that p is different to 50%, assuming the true value of p to be 80%, we require the number of participants in the subgroup

$(A+D+H+I+G+J+M+O+P+Q)$  to be 32 (based on an exact binomial test). Since this subgroup is an estimated 25% of the study population, we would need to recruit 128 participants

Assuming missing data of 10% of people recruited, our target recruitment will be 140. This original sample size calculation assumed that 50% of patients would proceed to medical therapy, and 50% to surgery. In the light of an observed asymmetry between these two group sizes, the total sample will be increased to 165.”

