### **12.1 Trial Sites and Numbers of Participants**

A total of 165 patients will be recruited into the study, from approx. three to six study sites within the UK depending on success on patient recruitment. Recruitment will continue until at least 70 patients have proceeded to adrenalectomy, even if we exceed a total of 165 patients being consented and undergoing investigations. This allows for some patients who may withdraw between consent and completion of investigations and/or surgery.

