**1.10.4. DEVIATIONS TO THOSE SPECIFIED IN STUDY PROTOCOL**

This SAP does not cover the analyses of data relating to 18F-CETO PET CT. A separate plan will be developed for this part of the study.

The primary outcomes specified in this SAP relate to the PASO criteria for biochemical and clinical cure. These are similar to, but more scientifically relevant than the primary outcomes specified in the current protocol.

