## **2.3. EFFICACY OUTCOMES**

### **2.3.1. PRIMARY OUTCOMES**

The primary outcomes will be analysed hierarchically. If the first primary analysis is statistically significant at  $p < 0.05$ , then the second primary outcome will be analysed; if the second primary analysis is statistically significant at  $p < 0.05$ , then the second primary outcome will be analysed; and so on. If any primary analysis fails to reach  $p < 0.05$ , then subsequent analyses will be considered secondary analyses.

Each primary outcome will be analysed in the subgroup of FAS patients who undergo surgery.

- Cure of hypertension at 6 months (non-inferiority analyses)
  - comparing accuracy of AVS and 11C-Metomidate PET-CT
  - each scan judged to be accurate if it indicated unilateral disease and cure of hypertension was achieved after surgery, or if the scan did not indicate unilateral disease and cure was not achieved after surgery
  - report estimated difference in accuracy (Newcombe-Wilson method for paired data) between 11C-Metomidate PET-CT and AVS, with 95% CI
  - non inferiority of 11C-Metomidate PET-CT will be declared if the lower limit of the above 95% CI is greater than -17%
  - each measure of cure (see Section 1.8) will be analysed in turn
- Cure of hypertension at 6 months (superiority analyses)
  - in addition to above, report p-value from exact McNemar test
  - superiority of 11C-Metomidate PET-CT will be declared if  $p < 0.05$ , and the lower limit of the 95% CI is greater than 0%

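### The stated 90% power with 32 discordant pairs does not hold for a two-sided exact test at 1% (it is 82.5%), and the SAP decides superiority at 5% without listing the change

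*Combined protocol and SAP*

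**What the plan says.** Protocol section 33.0 compares the two tests through the patients on whom they disagree. It takes a null of 50%, says that "the anticipated value of p is 80" per cent, and sets the requirement: "To have 90% power at a 1% significance level to show that p is different to 50" per cent. The subgroup needed is stated "to be 32 (based on an exact binomial test". The section continues "Since this subgroup is an estimated 25% of the study population" and derives 128 participants, then 140 after a 10% allowance for missing data. The protocol later raises the total to 165. SAP 1.5 reprints the calculation as the design-stage one and stops at 140.

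Three other protocol places bear on it:
- The synopsis gives 90% power at alpha 0.01 for superiority, with an estimated 90 adrenalectomies.
- Section 23.0 gives 90% power at alpha 0.01 with an estimated 70 adrenalectomies, but for non-inferiority within 16.7%.
- Section 12.1 sets the recruitment rule: "Recruitment will continue until at least 70 patients have proceeded to adrenalectomy".

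In SAP 2.3.1, "superiority of 11C-Metomidate PET-CT will be declared if" the exact McNemar p-value is below 0.05 and the lower 95% limit exceeds zero. SAP 1.10.3 says in general that its analyses differ from the protocol and that the protocol will be amended. SAP 1.10.4 lists two deviations: the CETO analyses are left out, and "The primary outcomes specified in this SAP relate to the PASO criteria for biochemical and clinical cure". It does not mention the significance level.

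**The concern.** The sample-size sentence names a test, a level, an effect and a power, so it can be checked directly. Its wording ("to show that p is different to 50%, assuming the true value of p to be 80" per cent) describes a two-sided alternative, and under that reading 32 pairs fall short of 90%.

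The SAP then prints a 1% sizing basis and a 5% decision rule in the same document. A superiority result with p between 0.01 and 0.05 would count as a success under the SAP but would miss the level on which the protocol was sized. A reader of the final report should be told that the level moved, when, and what power goes with the level used. The size of the operated group matters too, because all the information for this comparison comes from discordant operated patients.

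**Working it through.** **Inputs (table in section 33.0, % of recruits).** Cells favouring PET-CT: D+H+I+O+Q = 10+9+0.5+0.25+0.25 = 20. Cells favouring AVS: G+J+M+P = 1+3.5+0.25+0.25 = 5. So p = 20/25 = 0.80, and the discordant share is 25%. Both agree with the text. The printed subgroup also lists A (9%), which would make it 34%; the 25% actually used is the sum without A.

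Patients with at least one unilateral result are those offered surgery: C+D+G+H+I+J+K+L+M+O+P+Q = 56%. The discordant share of operated patients is therefore 25/56 = 44.6%.

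**Reproducing 32.** One-sided normal approximation: ((2.326×0.5 + 1.282×0.4)/0.3)² = 31.2, so 32. Exact, cutoff 23 of 32: P(X≥23 | 0.5) = 0.01003 and P(X≥23 | 0.8) = 0.910. The plan's figure is therefore a one-sided 1% calculation, met only after rounding the size.

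**The test as worded (two-sided exact 1%, n = 32).**
- Cutoff 23: two-sided size 2×0.01003 = 0.0201, too large.
- Cutoff 24: two-sided size 2×0.00350 = 0.0070. Power P(X≥24 | 0.8) = **0.825**.
- Holding a one-sided test strictly at or below 0.01 also forces cutoff 24 and gives 82.5%.
- The first n with 90% power is 39 (cutoff 28, 92.6%). Power dips to 89.8% at 41 and stays above 90% from 42.
- 39 pairs correspond to 39/0.25 = 156 evaluable patients, 156/0.9 = 174 recruited, or 39×56/25 = 88 operated.

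**Power with a random number of discordant pairs.** Power = Σ P(d pairs) × exact power at d, with d ~ Binomial(N, share) and p = 0.80.

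| Basis | Share discordant | Mean pairs | Two-sided 1% | Two-sided 5% |
|---|---|---|---|---|
| 32 pairs, fixed | – | 32 | 82.5% | 91.0% |
| 70 operated | 25/56 | 31 | 77.9% | 91.9% |
| 90 operated | 25/56 | 40 | 90.3% | 97.3% |
| 149 completers (section 16.6) | 25% | 37 | 86.8% | 95.9% |
| 165, all evaluable | 25% | 41 | 90.9% | 97.5% |

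**Sensitivity to the assumed share, 70 operated.** With 35% or 25% of operated patients discordant, power at 1% is 62% or 40%; at 5% the same sum gives 83% or 67%. These two shares are illustrative.

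**SAP scoring rule.** SAP 2.3.1 asks only whether each test indicated unilateral disease. M, O, P and Q then become ties, and C counts for AVS. So p = (D+H+I)/(D+H+I+G+J+C) = 19.5/25 = 0.78, with the share unchanged at 25/56. For 70 operated, power is 69% at 1% and 87% at 5%.

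**Consistency of 70, 90 and 165.** The table implies 165×0.56 = 92 operated, close to the synopsis's 90. Seventy of 165 is 42%, so the 165-patient row and the 70-operated row cannot both describe one trial on the table's proportions.

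**Loss allowance.** 128/0.9 = 142.2, so 143, not 140.

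**The case against.** The strongest reply is that the trial's actual superiority test has the power it needs. It runs at two-sided 5%, where 32 pairs give 91.0% and 70 operated patients give 87–92% on the table's proportions. At n = 32 the two-sided 5% test even uses the same upper cutoff, 23, as the one-sided 1% design. This stands. A reader might infer from the 82.5% that the planned test is underpowered; on the plan's own assumptions it is not.

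Second, 32 is not a blunder: it is what a one-sided 1% calculation gives to two decimals. This stands too. The defect is that sidedness is missing and the wording points the other way.

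Third, 32, 128 and 140 were superseded by 165, which gives 90.9% at two-sided 1% if every patient is evaluable. That is correct, but the protocol does not redo the calculation for 165, SAP 1.5 still prints 32 and 140, and section 16.6 works to 149 completers (86.8%).

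Fourth, it is tempting to say that the documents promise 90% superiority power with 70 adrenalectomies. They do not: section 23.0 ties 70 to non-inferiority, the synopsis ties superiority to 90, and section 12.1 makes 70 a floor. What remains is that the floor lets recruitment stop short of the synopsis's basis.

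Finally, the SAP does not hide that it departs from the protocol. SAP 1.10.3 says so and cites Steering Committee input. Only the itemised entry for the significance level is missing.

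**Conclusion.** Wrong as written; should be fixed. As a two-sided exact 1% test, 32 pairs give 82.5% power rather than 90%, and 39 pairs are the first number to reach 90%. The sizing level (1%) and the decision level (5%) differ, and neither SAP 1.10.3 nor 1.10.4 names that change. The 70 and 90 adrenalectomies are not reconciled: two-sided 1% power is about 78% at the first and 90% at the second.

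The 82.5% needs only the stated p and n. The figures by operated count also assume that the section 33.0 table holds, in particular that 25/56 of operated patients are discordant. They apply the table's endpoint (normalised renin and ARR) to the SAP's PASO outcomes and cover the McNemar condition only. Non-inferiority power was not checked.

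The documents do not support a claim that the trial is too small for the SAP's test, or that the level was changed covertly.

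**What to change.** State one significance level and its sidedness in protocol section 33.0, the synopsis, and SAP 1.5 and 2.3.1.

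- **If two-sided 5% is kept:** list it in SAP 1.10.4 as a change from the protocol's 1%. Replace the 1% power statement with about 87–92% for 70 adrenalectomies, and state the 25/56 discordance assumption beside it.
- **If 1% is kept:** change the SAP's superiority rule to p<0.01 with a 99% interval. Restate two-sided power as 82.5% for 32 pairs, about 78% for 70 operated and 90% for 90 operated.

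In either case, reconcile 70 with 90 adrenalectomies across the synopsis, section 12.1 and section 23.0, and carry the increase to 165 into SAP 1.5. Two small corrections belong in the same edit: remove A from the printed subgroup, and note that 128/0.9 is 143 (superseded by 165).

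The cost is wording only, with no extra patients or data. Under the 1% option the stated power falls unless the recruitment floor is brought up to about 90 operated. The edit should be made before the database is locked.
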